| Study Background Cardiovascular disease (CVD) is the leading cause of mortality worldwide.^1^ As a result, much healthcare resource is assigned to preventing CVD through modification of risk factors, such as raised blood pressure and/or cholesterol.^2^ This can be achieved through prescription of medications such as antihypertensives, statins and antiplatelets, which have been shown to be effective in reducing the risk of cardiovascular disease.^3-5^ These medications are often started when patients are at low-to-moderate risk and continued for many years, despite a low likelihood of benefit.^6^ Some patients who take these medications may suffer side effects such as falls, acute kidney injury (AKI), muscle pain and bleeding which can significantly reduce an individual’s quality of life, particularly those who are old and frail.^7-9^ Despite changes in an individual’s risk/benefit profile, clinicians are often reluctant to stop prescribing them.^10^  The association between cardiovascular preventative therapy and adverse events is not fully understood. This is due in part, to the completeness of reporting of side effects and adverse events in previous trials.^11 12^ Observational studies do show an association between treatment and adverse outcomes such as falls,^9 13 14^ AKI,^15^ myopathy,^16^ diabetes,^17^ and intracranial bleeding,^18^ but are limited in some cases due to small sample sizes and bias caused by unmeasured confounding. Observational data can however be useful since it allows multi-morbid populations to be examined, which are more representative of the general population than those enrolled into clinical trials.^19^  *Predicting the benefits and harms of treatment*  A structured approach to weighing up the risks and benefits of treatment is common in atrial fibrillation, where combining risk scores from the CHA_2_DS_2_-VASc tool^20^ and HAS-BLED tool^21^ allows one to compare an individual’s risk of stroke with their risk of a bleed. There are many other risk prediction tools which can be used to identify individuals who may benefit from CVD prevention treatment (i.e. are at high risk of CVD),^22-28^ but very few which can be used to identify those at risk of adverse events in the community. Existing tools show moderate discrimination and focus on patients with specific conditions and/or use in an acute hospital setting.^29-34^ None have been externally validated.^35-37^ Recent studies have described prediction models for the benefits and harms of *intensive* blood pressure lowering treatment,^38 39^ but these were derived exclusively from patients in the SPRINT trial,^7^ limiting their generalisability.  Stratifying treatments for prevention of CVD is important for UK and international health. Such an approach could facilitate shared decision making between patients and doctors and allow better targeting of treatments in settings where resources and access to drugs may be limited.  *How this project fits in*  This is one project in a larger work programme aiming to personalise preventative treatments for cardiovascular disease. In this project, we will quantify risks due to cardiovascular preventive treatments. In other projects, including systematic reviews, we will quantify and combine estimates of the benefits and harms of preventive treatments. This will enable us to develop a clinical decision tool to assist patients and their clinicians in understanding the relative benefits and harms of proposed treatment changes. |

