| Data/ Statistical Analysis **Prognostic modelling**  ***Aim 1 – prognostic model derivation (primary analysis)***  Where feasible and appropriate, flexible parametric survival models will be derived in the CPRD GOLD for each outcome separately. Baseline survival over time will be estimated using the Royston-Parmar approach of restricted cubic splines on the cumulative log hazard scale. In contrast to Cox regression, this allows a smoothed estimate of the baseline survival function to be derived, and the time period of prediction to be varied, facilitating individualised risk prediction. For the primary analysis, a 10-year period of prediction will be considered. Further sensitivity analyses will be conducted examining a 5-year period. Where insufficient data are available, or modelling procedures become prohibitively complex (computationally), simpler approaches such as Cox regression will be considered.  Each drug class (prescribed in the 12 months prior to the index date) will be entered into the model as a binary variable to allow for multiple treatments to be considered in each model. Where appropriate, models will be constructed with all other variables entered as continuous (not categorised) variables, and potential non-linear trends will be examined. Transformations or fractional polynomials will be used if non-linear trends are detected. Where hazard ratios are not proportional, interactions of effects with time will be included. Further interaction terms, identified in an accompanying systematic review, accounting for treatment effects which differ across specific populations may be included. Where appropriate, models will be reduced and candidate predictors selected for inclusion based on p values of association. Time since cohort entry will be used as the underlying time function in each survival model.  In a further analysis, we will extend the modelling process as described above to account for competing risk of death from other causes. This will produce a model that predicts the risk of adverse events from cardiovascular treatment over time, in the real world where individuals might die from other causes and thus prevent cardiovascular treatment adverse events from occurring. We will again use a flexible parametric modelling framework to estimate the sub-distribution hazard and cause-specific cumulative incidence functions.^45^  Missing data will be handled, under a missing at random assumption, using multiple imputation (see below) followed by Rubin’s rules to combine parameter estimates across studies.  Where feasible and appropriate, each model will be internally validated using the bootstrap method, to allow optimism-adjusted estimates of calibration and discrimination performance to be obtained. Adjustment for overfitting will be undertaken using a uniform shrinkage factor identified from bootstrapping, followed by re-estimation of the cumulative baseline sub-distribution hazard function (and thus baseline cumulative incidence function) to maintain overall calibration between observed and predicted risks. Given the large sample size, overfitting is likely to be small (see sample size calculation above). If bootstrapping is computationally infeasible due to the large sample size, then a smaller random sample of the population will be used or alternative internal validation methods employed such as cross validation.  ***Aim 2 – prognostic model validation***  External model validation will be undertaken using data from CPRD Aurum. The accuracy of risk predictions from each model will be assessed with calibration plots and 5 and 10 years, calibration measures (slope, E/O statistics), measures of overall fit (using pseudo-R^2^ estimates) and discrimination measures (C-statistics and D-statistics).  ***Aim 3 – causal inference analysis***  For most of the outcomes described in this proposal, the association and magnitude of effect with treatment is not well defined in randomised controlled trials. We will therefore undertake causal inference work to examine whether modification of treatment could have an important impact on the risk of adverse events using two causal inference methods: propensity score matching and instrumental variable analysis.  For the propensity score analysis, eligible patients will be matched 1:1 at the index date using propensity scores, which indicate the likelihood a patient will be prescribed treatment on the basis of their known (pre-treatment) characteristics and other known information which might influence the decision to treat. Predictors of preventative drug prescription will be explored in a logistic regression model. Matched patients will be compared using the Cox proportional hazards models, but hazard ratios will only be adjusted by factors unbalanced at baseline which are not already included in the propensity score model. Time since cohort entry will be used as the underlying time function in each model.  For the instrumental variable analysis, GP’s previous antihypertensive prescribing preferences will be used as an instrument to predict the likelihood of actual treatment. Risk of adverse events will be estimated in patients attending a GP considered a high prescriber of preventative medication and compared to those attending a GP considered a low prescriber. If the results from the propensity score matching suffer from unmeasured confounding, they will differ from those of the instrumental analysis. If this is the case, these models will be refined with additional factors to achieve better adjustment and matching. Where all approaches provide similar results, we can be more confident that the findings are accurate and reliable.^46^  A similar approach will be applied to secondary outcomes, for example, memory loss which has been hypothesised as being linked with statins^47^ and is a concern of many patients in practice, but there is no evidence to support this association from trials.^48^ We recognise that the evidence base may change for some outcomes over the next few years, and so the need to test the associations between treatment and certain outcomes may change.  *Subgroup and sensitivity analyses*  Where possible and appropriate, analyses of treatment associations will be examined in subgroups of the population. These will include age, sex, baseline blood pressure and cardiovascular risk, by drug type/dose/intensity and past medical history. Subgroup definitions will be agreed by expert opinion or taken from an accompanying systematic review of previous trials, examining the same topic.  Sensitivity analyses will be undertaken examining risk models for outcomes defined according to both hospital and primary care records. We will also explore the impact of our definition of myopathy and muscle pain, focussing on formal diagnostic codes for myopathy only. Models utilising a 5-year follow-up will be examined as a further sensitivity analysis. The primary analyses will examine the association between treatment and outcomes, assuming treatments are not altered or modified in the future. Where possible, sensitivity analyses will examine treatment entered as time varying covariates, and censor patients who have treatments removed or switched following the index date. |

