| Plan for addressing confounding Two approaches will be taken to determine whether observed associations are potentially subject to residual confounding.^46^ Where all approaches provide similar results, we can be more confident that the findings are accurate and reliable. Further steps will be taken to examine the validity of treatment effect estimates using positive and negative controls: the impact of treatment on an outcome known to be affected by treatment (e.g. cardiovascular disease; positive control) and outcomes not known to be affected by treatment (negative control). Here, we will combine two common but unrelated outcomes to be examined as negative controls: bowel cancer and chronic obstructive pulmonary disease (COPD). If treatment has a significant impact on these negative controls, it suggests that there is something missing in the analysis (i.e. an unmeasurable factor confounding the treatment effect such as being generally unwell or an unhealthy lifestyle) causing an imbalance between the treatment and control groups, rather than a true treatment effect. |

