| Limitations of the study design, data sources, and analytic methods This study focuses on potential harms from adverse events associated with preventative treatments for cardiovascular disease. Such outcomes may be less well recorded in routine electronic health records. For example, initial scoping work suggests the rate of falls documented in the CPRD is between 0.06-0.34% per 1000 person-months. These incidence rates may be less than those reported in smaller previous studies (0.15-6.40% per 1000 person-months) using different definitions, captured via detailed questionnaires and follow-up.^49-52^ Incidence rates are likely to be higher when linked data from HES and ONS are available.^53^ Missing data on certain outcomes may reduce the accuracy of the prognostic models, but should not bias the results provided the data are missing at random and not affected by whether patients are prescribed treatment. To minimise the risk of reporting bias, outcomes in the primary analysis will be defined according to hospital admissions documented in the HES or ONS.  The causal inference work will use an observational cohort design, and as such, there is an inherent selection bias of patients in both exposure and control groups. The impact of this bias will be limited by propensity score methods used to control for confounding, but this approach assumes that all confounding factors are measured and accounted for within the analysis. In the present study, we will examine the validity of this assumption by 1) using an instrumental variable (GP prescriber preference) and examining the association with the outcomes of interest and 2) by studying the impact of treatment on positive and negative controls: hospitalisation and/or death from cardiovascular disease and bowel cancer/COPD. We will conclude the assumption has been met if high GP prescribers have a similar association with outcomes and the treatment itself and treatment is shown to be associated with the positive control, but not the negative control.  *Strategy for dealing with potential errors resulting from multiple testing*  This study will examine multiple outcomes across 3 exposure variables. To avoid potential errors arising from multiple testing, a primary outcome has been clearly defined for each exposure variable. Secondary outcomes are also pre-specified. The primary outcome will be given priority in the final analysis write-up and any related reports and presentations.  Primary and secondary outcomes will be defined using data from Basic inpatient HES and ONS. Sensitivity analyses will explore analyses defining these outcomes using the above sources and read-coded primary care data. The accuracy of such outcome data has been examined previously in patients with acute myocardial infarction and whilst recording of risk factor and co-morbid information was consistent across primary care, hospital admissions and disease registry records, the crude incidence of acute myocardial infarction was underestimated by up to 50% if only one data source was used, compared with using all three sources.^53^ The use of linked CPRD data will ensure outcome data are ascertained accurately. |

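### The protocol's rule for concluding that there is no unmeasured confounding can accept a confounded result: the positive control has no direction, the negative control is judged by significance, and propensity models may be refined after outcome results are seen

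*Protocol*

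**What the plan says.** The rule stands in the Limitations section of the Protocol: "We will conclude the assumption has been met if high GP prescribers have a similar association with outcomes and the treatment itself", and if "treatment is shown to be associated with the positive control, but not the negative control". Three other places supply its parts.

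- **Positive control.** Plan for addressing confounding describes it as "the impact of treatment on an outcome known to be affected by treatment (e.g. cardiovascular disease; positive control"). Amendment 2 adds death as a second positive control. Neither place states a direction. The direction for cardiovascular disease appears only in the Study Background, which says of these drugs "which have been shown to be effective in reducing the risk of cardiovascular disease".
- **Negative control.** The same section says "we will combine two common but unrelated outcomes to be examined as negative controls: bowel cancer and chronic obstructive pulmonary disease (COPD"), and the criterion is significance: "If treatment has a significant impact on these negative controls, it suggests that there is something missing in the analysis".
- **Propensity score against IV.** Data/Statistical Analysis, Aim 3, says that unmeasured confounding will show as a difference between the two results. If they differ, "these models will be refined with additional factors to achieve better adjustment and matching". Similar results across approaches are then grounds for more confidence. Amendment 3 reprints this text.

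Sample size considerations sets the effect of interest for the causal analyses at a 10% increase in the event rate.

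**The concern.** A control-outcome check is useful only if it fails when the analysis is confounded. Each leg of this rule has a weakness.

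Confounding by indication, which Amendment 3 names as a problem to be dealt with, gives treated patients more cardiovascular disease. If it is strong enough to reverse the protective effect, treatment is still associated with the positive control, and the leg is met by the failure it should detect.

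A non-significant negative control does not show that bias is absent. With few events a bias as large as the target effect can pass; with very many, a negligible one fails.

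When the propensity model is changed because its outcome result differs from the IV result, agreement afterwards is no longer independent support. The two can also differ without any confounding.

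At stake is the sentence certifying the Aim 3 treatment-effect estimates. The prediction models of Aims 1 and 2 are not affected.

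**Working it through.** **Inputs from the Protocol.** HR 1.10, 90% power, alpha 0.05, 0.5% per year in the unexposed, 4,634 events and 88,380 patients (Sample size considerations); 1:1 matching (Aim 3). **Assumptions.** All control-outcome event counts, bias sizes and prescribing differences below; the Protocol gives none.

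**1. The plan's own figures.** Freedman, two-sided: D = (1.960 + 1.282)² × [(1 + 1.10)/(1 − 1.10)]² = 10.507 × 441 ≈ 4,634, as stated. With 10 years at 0.5%, p0 = 0.05 and p1 = 1 − 0.95^1.1 = 0.05486, so N = 2 × 4,634/(0.05 + 0.05486) = 88,384, against 88,380 stated. The 10 years is inferred, since the Protocol states that horizon only for the prediction models. The sample size is not in dispute. It supplies 4,634 as a reference count.

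**2. Positive control.** With 1:1 groups, SE(log HR) ≈ 2/√D. Assume a true cardiovascular HR of 0.80 and D = 4,634.

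| Bias factor | Observed HR | P(significantly associated) | P(significantly protective) |
|---|---|---|---|
| 1.00 | 0.80 | about 1.00 | about 1.00 |
| 1.25 | 1.00 | 0.05 | 0.025 |
| 1.50 | 1.20 | about 1.00 (z = ln 1.20 × √(4,634/4) = 6.2) | about 0 |

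This leg usually rejects the moderate bias and accepts the larger one.

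**3. Negative control.** The largest HR still called non-significant is exp(1.96 × 2/√D). The chance that a purely spurious HR b passes is Φ(1.96 − m) − Φ(−1.96 − m), with m = ln b × √(D/4).

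| Assumed events D | Largest non-significant HR | P(pass), b = 1.05 | P(pass), b = 1.10 |
|---|---|---|---|
| 500 | 1.19 | 0.92 | 0.81 |
| 1,000 | 1.13 | 0.88 | 0.67 |
| 4,634 | 1.06 | 0.62 | 0.10 |
| 20,000 | 1.03 | 0.07 | about 0 |

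At 30,000 events the limit is 1.02. The verdict therefore tracks D as much as the size of the bias.

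**4. Propensity score against IV.** Aim 3 compares patients of high and low prescribers. If that contrast is not rescaled for treatment actually received, it is diluted. Assume 20% and 40% treated and a true rate ratio of 1.10. The contrast is (1 + 0.10 × 0.40)/(1 + 0.10 × 0.20) = 1.04/1.02 ≈ 1.02. An unconfounded propensity estimate of 1.10 would then differ from the IV result, and moving it towards 1.02 would introduce bias.

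**The case against.** The strongest reply is that the three conditions apply jointly. Confounding large enough to reverse the cardiovascular result would also have to escape the negative control and leave the IV result similar. That stands: a reader might infer that the rule would pass a confounded result as a matter of course, but the wording supports only that it can.

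The protective direction can be guessed from the Study Background. True, but the rule does not apply it, and the rule is what licenses the conclusion.

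The event counts are assumed. The Protocol calls the negative controls common and expects about 3.3 million eligible patients, so 500 events may be too few for the larger cohorts. At 4,634 events the limit is 1.06, below the 10% target. That also stands, and it is why a range is shown. It does not rescue a criterion whose answer depends on the count.

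A reader might infer that the propensity model will be refitted until it matches the IV. The text does not say so: its stated aim is better adjustment and matching, and no loop is described. What it does fix is that the trigger is an outcome result, and it sets no limit on refits and no exploratory label. Amendment 2 also adds a Cox analysis adjusted for pre-specified variables, which gives a comparator outside this refitting. Amendment 3 then reprints the older two-method text, so how the methods fit together is not fully clear.

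A reader might also argue that bowel cancer and COPD are unsuitable for antiplatelets, because gastrointestinal haemorrhage and dyspnoea are listed harms. The documents list those outcomes but do not show the link. A negative control need only be unaffected by treatment.

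Finally, margins and model locking often belong in a statistical analysis plan. Here, though, the Protocol itself fixes the rule for the conclusion.

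**Conclusion.** The point holds in this form: as worded, the rule can declare the no-unmeasured-confounding assumption met for a confounded Aim 3 estimate. The missing direction and the outcome-triggered refinement follow from the wording alone. The size of the negative-control weakness rests on assumed 1:1 event counts and a normal approximation to the log HR. A spurious HR of 1.05, half the target effect, passes that leg 62% of the time at 4,634 events and 88% at 1,000. At 20,000 events it passes only 7% of the time, and a trivial bias may fail instead. These are probabilities for single legs, not for the whole rule. The documents do not show that any estimate will in fact be confounded.

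**What to change.** 1. **Positive control.** Require the cardiovascular HR to be below 1, and state in advance what is expected for death. Direction alone catches only a reversal. A protective effect weakened by confounding would still pass.
2. **Negative controls.** Report bowel cancer and COPD separately as well as combined, since a pooled result can hide bias in one of them. Judge each by its HR and 95% CI against the 10% effect of interest. Call the check inconclusive when the CI does not exclude bias of that size, and drop non-significance as the criterion.
3. **Propensity score and IV.** Settle the propensity model on covariate balance before outcomes are analysed. Report the pre-specified propensity and IV estimates with a CI for their difference. Label any later refit exploratory, and do not count it as evidence of agreement.

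**Cost.** Protocol wording and a few extra control-outcome models. The real price is inconclusive checks. Even with an observed HR of exactly 1.00, the upper 95% limit falls below 1.10 only if D > (3.92/ln 1.10)² ≈ 1,692 events. So a cohort with 500 or 1,000 events cannot show that bias of this size is absent in both directions (taking 1/1.10 as the lower bound). With no bias and 4,634 events, the estimate must lie within ln 1.10 − 3.92/√4,634 = 0.0377 of zero on the log scale. That is 1.28 standard errors, so the check succeeds about 80% of the time. A tighter margin of 0.95 to 1.05 is not proposed: by the same formula it needs about 6,455 events per control outcome, (3.92/ln 1.05)².
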